### Data collector training

Local CHVs were hired to supplement the Mashinani team for data collection and intervention implementation. The data collection team underwent a month-long training process that covered data collection procedures, app content and procedures, tablet orientation for delivering the myPlan Kenya app, survey measures, and ethical training, including that specific to research on gender-based violence [43], with mock data collection and intervention sessions.

### Recruitment of participants

Eligible women were ages 18–35 years-old, had experienced physical or sexual IPV, or reported being afraid of their partner in the last three months, resided in Korogocho/Kariobangi, Dandora, or Huruma/Mathare with no plans to move in the next six months, and spoke English or Swahili language. Community-based recruitment occurred through flyers, community presentations, and word-of-mouth. This passive recruitment method is a sensitive way to recruit IPV survivors, allowing them the opportunity to decide on study participation without feeling pressured.

Local CHVs aided in raising awareness about the study and referring potential participants. Recruitment events held specifically with CHVs informed them of the study objectives and sought feedback on recruiting eligible women. CHVs then worked in tandem with the recruitment team to refer potential participants. Study participants were also offered recruitment flyers to notify others about the study. Recruitment continued until adequate sample size achieved in each of the three sites with an enrollment goal of 350 women. The study process is outlined in Fig. 1.

**Fig. 1 Fig1:**
[figure not shown]
Study process diagram, including time points for assessment and enrollment

### Informed consent and enrollment

Participants contacted study staff by telephone or in person for more information about the study and pre-screening. Research staff clarified the purpose and parameters of the study, and eligibility criteria. Eligible participants were then invited to their preferred site for in-person data collection.

On-site eligibility confirmation via tablet occurred in private immediately prior to consent. Age and residence criteria were confirmed via single questions. Recent IPV or partner-related fear criteria were assessed via three items with “yes” to any satisfying eligibility criteria: 1) “Is there something about your partner that makes you feel unsafe or threatened?”; 2) “In the past 3 months, did your partner hit, punch, throw, slap, or kick you?” and 3) “In the past 3 months, did your partner ever force or pressure you to have sex when you didn’t want to?”

An oral consent process maximized participant confidentiality. To verify and document consent, the data collector initialed and dated the consent form saved within the tablet by study ID.

### Randomization to intervention or control condition

Following tablet-based baseline survey data collection, women were randomized to either the control or intervention arm within the app itself, stratified by study site (1:1 allocation); following randomization participants were seamlessly directed to either the control or the intervention app. The tablet further eased data collection given recording of all consent, survey data, and app measures, as well as analytics on time-to-completion and missingness of data. Intervention participation took approximately 30–45 min, whereas the control condition was limited to 10–20 min.

### Blinding

All participants were blinded. Study staff aiding participants with the app were necessarily nonblinded; all other study staff, including those involved in recruitment, enrollment/consent, warm referrals, and data monitoring, were blinded to intervention status.

### Baseline data collection

Survey data collection preceded randomization and took approximately 30–45 min. Interviewer-facilitated survey data collection and app assistance was recommended in the formative phase to maximize comprehension and interest. While some participants preferred to complete the survey almost entirely on their own, others made use of the available assistance from trained study team members. All data collection was recorded on a tablet to allow the use of on-screen buttons and clickable sliding bars, as well as audio visual to enhance interaction.

## Measures

### Primary outcomes

Primary outcomes include safety preparedness, decisional conflict, use and helpfulness of safety strategies, and IPV.

A 10-item scale assessed safety preparedness immediately following completion of intervention or control condition. Items focused on the value of the reviewed material for readiness in decision-making and weighing of risk/benefits, e.g., “to what extent did the material prepare you to make safety decisions,” with participants indicating preparedness on a Likert scale (Responses: 0-Not At All to 4-A Great Deal; Range: 0–40; modelled continuously).

A 12-item adaptation of the Decisional Conflict Scale (DCS), which discriminates those who make decisions and those who delay [44], asked participants to rate their knowledge, clarity and confidence in safety options and risk/benefits of potential options on a Likert scale [30] (Responses: 0-Not At All to 4-A Great Deal; Range: 0–48; modelled continuously).

Use of safety strategies was assessed through five-item index of strategies specific to content area covered in the app; the index was adapted from previous myPlan trials and formative work in the U.S. [26, 30, 45] Specifically, participants were asked “In the past three months, have you: 1) Left the house temporarily to put space between you and your partner; 2) Developed an emergency signal to use with others when you felt you were in danger; 3) Put a plan into place for how to keep your children safe; 4) Begun saving money to build self-sufficiency; and 5) Been part of a loan savings group in order to improve your family’s financial situation. If used, participants were then asked to rate the helpfulness of the strategy on a Likert scale (Responses: 1-Not Helpful to 5-Very Helpful). Responses generated two summary metrics: use of safety strategies reflecting number of strategies used (Range: 0–5), and helpfulness of strategies used, reflecting both use and helpfulness by dividing summed helpfulness by number of strategies used (Range: 0-Never Used to 5-Used and Found Helpful).

Longer-term outcomes focused on IPV experiences. Physical and sexual IPV were assessed through the short forms of the Revised Conflicts and Tactics Scale (CTS-2) [46]. For each of ten violent behaviors, women were asked frequency of occurrence in the past 3 months: Never (0), 1–2 times (1), 3+ times (2), and scores summed across behaviors (Range: 0–20); IPV will be examined as both continuous and binary for physical IPV only, sexual IPV only, and combined physical and sexual IPV. The Women’s Experiences of Abuse (WEB) Scale [47] captured the lived experience of abuse (Responses: 1-Agree Strongly to 6-Disagree Strongly; Range: 10–60). Reproductive coercion was assessed via existing 9-item measure [48, 49] deemed appropriate based on formative research and summarized into a binary measure indicative of experience/no experience. All IPV assessments used behavioral definitions in accordance with best practices [43].

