**Methods:**

A community-participatory formative process engaged service providers and stakeholders, as well as IPV survivors for adaptation, followed by an in-depth pilot and final refinements. A randomized clinical trial design will then be used to determine efficacy of the myPlan Kenya app compared to standard care among women reporting IPV or fear of partner and living in an urban settlement. myPlan Kenya app provides and solicits information on a) relationship health; b) safety priorities; and c) severity of relationship violence. Based on the woman’s inputs, the evidence-based algorithm developed for myPlan Kenya generates a tailored safety plan. Outcome measures are assessed at baseline, immediate post-intervention, and 3-month post-baseline. Difference-in-differences analysis compares primary (e.g. safety preparedness, safety behavior, IPV), and secondary outcomes (e.g. resilience, mental health, service utilization, self-blame) across timepoints by group.

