## Randomized controlled trial methods

### Design

This trial is designed as a randomized, controlled, participant-blinded superiority trial with two parallel groups (1:1 allocation ratio), with primary end points of safety preparedness, decisional conflict (e.g. clarity of values, knowledge), use and helpfulness of safety strategies, and IPV.

We hypothesized women in the myPlan Kenya safety decision app group would have increased safety preparedness, reduced decisional conflict about safety priorities, increased helpfulness and use of safety behaviors, and reduced IPV at three-months post-baseline in comparison to the control group.

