### Intervention efficacy

All analyses will be performed using intent-to-treat principles. Primary analysis uses a differences-in-differences approach to compare differences between baseline and 3-month follow-up by intervention group. Random effects logistic and linear regression models will be created, including study arm, pre/post status and their interaction term (study arm*pre/post status). Interaction terms significant at *p*-value < 0.05 will indicate a significant intervention effect.

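### Safety preparedness, a primary endpoint, can have no baseline value, so the primary difference-in-differences analysis cannot be estimated for it

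*Protocol article*

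**What the plan says.** All references are to the protocol article.

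- **Status.** The Primary outcomes section states: "Primary outcomes include safety preparedness, decisional conflict, use and helpfulness of safety strategies, and IPV".
- **Timing and content.** The same section says: "A 10-item scale assessed safety preparedness immediately following completion of intervention or control condition". Its example item asks "to what extent did the material prepare you to make safety decisions", and the score is described as "Range: 0–40; modelled continuously".
- **Baseline.** Under Baseline data collection: "Survey data collection preceded randomization and took approximately 30–45 min". The Randomization section sends women to their app only after that survey and the allocation.
- **Primary analysis.** Under Intervention efficacy: "Primary analysis uses a differences-in-differences approach to compare differences between baseline and 3-month follow-up by intervention group". The models contain arm, pre/post status and their interaction, and an interaction p-value below 0.05 is the criterion for an effect. No outcome is exempted.
- **Abstract, Methods.** "Difference-in-differences analysis compares primary (e.g. safety preparedness, safety behavior, IPV", so this endpoint is the first example given for that analysis.
- **Hypothesis.** The Design section begins "We hypothesized women in the myPlan Kenya safety decision app group would have increased safety preparedness, reduced decisional conflict about safety priorities", goes on to safety behaviours and IPV, and has a three-month time phrase at the end of the list.

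**The concern.** A difference-in-differences needs a pre-exposure value in each arm. A scale that asks how far the material helped cannot be given to a woman who has not yet seen any material. The plan therefore assigns to a named primary endpoint an analysis, and a criterion of success, that cannot be computed.

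The estimator for that endpoint would then have to be chosen outside the stated plan, possibly after the data have been seen. That is a poor position for any primary endpoint. It matters more here because the article lists several primary outcomes, and this one is named first.

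**Working it through.** **1. Which cells exist.** The planned contrast for an outcome Y, with arms I (intervention) and C (control), is

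DiD = (Y_I,3m − Y_I,0) − (Y_C,3m − Y_C,0).

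For safety preparedness, Y_I,0 and Y_C,0 would have to come from the baseline survey. That survey precedes randomization and all app content, and the items refer to the content. Both cells are empty by construction. The article's imputation rule does not help: it covers variables with under 10% missing, and here 100% of baseline values are missing.

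**2. Can the interaction be estimated?** The model is E[Y] = b0 + b1·arm + b2·time + b3·arm×time, with effect parameter b3.

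- With baseline and 3-month data, the four arm-by-time rows (1,0,0,0), (1,0,1,0), (1,1,0,0) and (1,1,1,1) have rank 4 for 4 parameters. b3 is estimable.
- With post-session data only, the rows are (1,0,1,0) and (1,1,1,1). The time column equals the intercept, and arm×time equals arm. The rank is 2 for 4 parameters. Only b1 + b3, the post-session difference between arms, is estimable.

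**3. Would a 3-month repeat rescue it?** No. The baseline cells remain empty. Using the immediate score as the pre value would not give the planned effect either, because that score is already affected by allocation. If the app raised the score by d at both times, the contrast would be d − d = 0. It would measure change after the session, not the effect of the app.

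**4. The plan's own sample size.** The Statistical power section powers on IPV only: 39% against 25%, alpha 0.05, power 0.80, 175 per arm. Taking alpha as two-sided, with pooled variance and no continuity correction:

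n = [1.960·√(2·0.32·0.68) + 0.842·√(0.39·0.61 + 0.25·0.75)]² / 0.14² = (1.293 + 0.549)² / 0.0196 ≈ 173.1, rounded up to 174 per arm.

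Power with 175 per arm is 0.804. The stated figure reproduces and is not affected by this point.

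**5. What the estimable comparison can detect.** For a between-arm comparison of one continuous score at 80% power, two-sided 5%:

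detectable difference = (1.960 + 0.842)·√(2/175) = 2.802 × 0.1069 ≈ 0.30 SD.

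If the 15% attrition allowance applied (about 149 per arm), it would be 2.802 × √(2/149) ≈ 0.32 SD, although 3-month attrition need not touch a same-day measure. The article gives no standard deviation for the scale, so this cannot be put in scale points.

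**The case against.** The strongest reply is that the article already contains a suitable comparison. The Data analyses section provides t-tests or ANOVA between groups for continuous outcomes and says that all analyses account for site, which is close to the remedy proposed here. That is true, and a plan to compare the arms directly is not wholly absent. But the paragraph opens as work done before the analyses, does not name safety preparedness, and covers outcomes and potential confounders together. The efficacy section that follows gives one criterion, the interaction, and exempts nothing.

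A second reply is that the abstract names this endpoint for difference-in-differences across time points generally and does not itself specify the baseline-to-3-month contrast. That is also true; the contrast comes from the Intervention efficacy section. Since no pair of time points includes a pre-exposure score, the conclusion does not change.

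Two stronger readings are tempting and go beyond the text:

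- A reader might infer that the scale was given only once. The article does not say so. Its abstract lists three assessment occasions for outcomes in general, and the schedule in Fig. 2 is not available here.
- A reader might infer that the preparedness hypothesis is wrongly set at three months, so that a same-day rating would be reported as a three-month effect. The time phrase in the Design section may govern the whole list or only IPV, which the article elsewhere treats as the longer-term outcome. The sentence is ambiguous, not demonstrably wrong, and no such report is planned in the text.

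Finally, endpoint-specific models often sit in a statistical analysis plan that is not shown. That would answer a complaint about missing detail. Here an analysis is stated, and it cannot be applied to the endpoint as described.

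**Conclusion.** The point holds. For safety preparedness the stated primary analysis is not estimable: its effect parameter does not exist without pre-exposure scores, and the nature of the items rules such scores out. This rests on the article's own account of item content and on the order of survey, randomization and app. It does not depend on Fig. 2 or on how the hypothesis sentence is read.

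The consequence is limited to this endpoint. The post-session comparison of randomized arms is valid, the sample size is unchanged, and the other primary outcomes are not touched by this point. It still needs correcting, because a primary endpoint cannot be analysed as written and no other analysis is designated for it.

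**What to change.** 1. In Intervention efficacy and in the abstract, exempt safety preparedness from the difference-in-differences.
2. Designate as its primary analysis a between-arm comparison of the immediate post-session score, by linear regression on arm and site, in all randomized women under the intention-to-treat principle already stated.
3. In Design, state that the preparedness hypothesis refers to the immediate post-session assessment. If the schedule in Fig. 2 also includes a 3-month administration, say which time point is primary. A 3-month score would likewise be compared between arms directly, not as change from baseline.
4. In Data analyses, make clear that the general between-group tests are preliminary and do not replace item 2.

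The cost is a few sentences of wording. No data, visits or change in sample size are needed. The choice should be recorded before outcomes are compared by arm or, if that has already happened, reported as a dated change to the plan.

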### Secondary outcomes

Secondary outcomes include resilience, relationship quality, depression, consideration and seeking of IPV support services, self-blame, recognition of abuse, self-efficacy, and danger score.

Resilience was assessed with the ten-item Connor-Davidson Scale [50], which has been validated in East Africa [51] (Responses: 0-Not True At All to 4-True Nearly All the Time; Range: 0–40; modelled continuously).

Relationship quality was assessed with four items adapted from the CTS-2 negotiation sub-scale [46] deemed most applicable by the field team. Respondents rated frequency of respectful relationship experiences on a 4-response Likert Scale (Responses: 0-Never to 3-Almost Always; Range: 0–12). Responses were summed and modelled continuously.

Depression was assessed through the 10-item Center for Epidemiologic Studies Depression Scale (CESD-R; Responses: 0-Not At All/Less Than 1 Day to 3-Nearly Every Day; Range: 0–30) [52, 53] and modelled both continuously and dichotomously with a score > =10 indicating clinical depression.

Support service consideration and use, respectively, were assessed via a select-multiple item asking “In the past three months, have you considered seeking any of the following for partner-related violence or fears?“ [30, 45] Multi-select options included health, emergency, police/chief, legal, crisis hotline, counseling, housing, and children, based on previous myPlan trials and services identified during the formative phase. Participants endorsing having considered a given service were subsequently asked if they had sought that service. The outcome was handled dichotomously overall and for individual response; per item, a positive indication to any response was considered positive “considering” or “seeking.”

Self-blame was assessed through a 4-item adaptation of the characterological sub-scale of the Sexual Victimization Attributions Measure (SVAM) [54]. Frequency of self-doubt and blame was measured on a 5-response Likert scale (Responses: 0-Never to 4-Almost Always), and summed for a continuous metric (Range: 0–12).

Six recognition of abuse items were adapted from the Abusive Behaviors Scale [49, 55]. Items asked participants to consider six abuse behaviors on a 5-point Likert scale from 0 (Not Abusive at All) to 4 (Very Abusive). Items were summed and modelled continuously (Range: 0–24).

The 6-item Generalized Self-Efficacy Scale [56] includes broad statements about confidence, goalsetting, and coping (Responses: 1-Not True At All to 4-Exactly True; Range: 6–24). A 4-item Self-Efficacy for Safety in Relationship Scale [31] specifically examines confidence in relationship safety (Responses: 1-Strongly Disagree to 5-Strongly Agree; Range: 4–20). Both measures were summed for continuous modelling.

A 20-item Danger Assessment (DA) Scale [33] assessed homicide risk factors (Range 0–20). Items were only asked of intervention participants within the myPlan Kenya app.

### Description of the myPlan Kenya intervention app

The intervention app was CHV-administered based on formative phase input that suggested women would prefer to use the app at least once with a supportive volunteer or provider before using it on their own. The myPlan Kenya app included the following sections: Healthy Relationships, My Relationship, Red Flags, My Safety, My Priorities, My Plan, About Violence, Harmful Beliefs About Abuse, and Resources. Healthy Relationships is an educational component to help women think about their relationship and what constitutes a healthy relationship within their context. My Relationship gathers information about their relationship to help tailor safety strategies. Red Flags helps women understand and assess warning signs of abuse within their relationship. At the end of the section, women are given a healthy relationship score (healthy, unhealthy, vs. unhealthy/unsafe) based on their responses. Safety strategies are also tailored to these individual items of abuse. My Safety is a danger assessement [33] consisting of validated risk factors for repeat violence and severe/lethal IPV, such as an increase in frequency/severity of violence, controlling behaviors, and weapon use. An instant danger assessment score is computed and converted to a level of danger (increased vs. variable) to prompt action for women at high levels of danger. The My Priorities section is an interactive visual aid that uses a clickable “sliding bar” to allow the participant to make pairwise comparisons to weigh priorities including dignity and respect, feelings for partner, health, and children. These priorities are combined mathematically to generate priority weights that are reviewed by users before moving on to the My Plan/safety plan section. The My Plan section is populated based on data supplied in the previous sections. For example, for women indicating children as a priority, the personalized safety plan messages include safety strategies specific to managing children in situations of violence. The safety plan is followed by supplemental information About Violence, Harmful Beliefs that may hinder their plan, and relevant Resources.

### Intervention Fidelity

Comprehensive training for the entire study team emphasized delivery of identical procedures for intervention and control participants. Randomization to either intervention or control app was completed automatically on the tablet to maximize fidelity and minimize error. Once a participant was randomized, the tablet did not allow switching of intervention condition. The app-based format maximized fidelity in intervention implementation. Intervention fidelity was further monitored by both JHU and Mashinani team members through an online tracker to ensure 1:1 enrollment and completion of each condition. Referrals were provided by a designated referral team to ensure that both intervention and control participants received the same standard set of referrals, regardless of experience disclosed during the survey or intervention condition.

